### Intervention

This is a complex intervention that includes the training of FPs and physician-patient interview based on the Ariadne principles; the effectiveness of the intervention has been studied in the MULTIPAP RCT [23, 36, 37]. The training includes activities related to basic concepts of multimorbidity, the appropriateness of prescriptions, adherence to treatment, the ARIADNE principles, and shared doctor-patient decision-making. All participating physicians will receive this training with the objective of incorporating patient-centred interviews into their routine clinical practice. This would allow the effect of the training to be isolated from the use of a DSS.

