#### Intervention group

Several key elements of the intervention must be highlighted:
Clinical data will be reviewed and registered by FPs in the electronic case report forms (eCRF) after recruitment in baseline visit.Because of the natural separation between actual electronic health records and electronic case report forms developed for the research project, final tool has been integrated into a dedicated eCRF system using a webservice WS4 version 1.2 of the CheckTheMeds® tool with the specific inputs reviewed by the FPs. This avoids barriers for FPs and the need for reintroducing double information to a separate system. Simple and detailed review of treatment plans has been incorporated. Simple review webservice outputs have been agreed after a Delphi technique with relevant stakeholders (primary care pharmacist, hospital pharmacist, family physicians, and researchers).The web-based, user-initiated DSS provide FPs with drug-therapy information that is relevant to participating patients with polypharmacy on demand. After verifying the clinical data included in the eCRF (multimorbidity and polypharmacy corrected for patient-specific factors such as sex, renal function, age and frailty), this DSS provides health professionals with clinical scenarios to optimize treatment plans for patients, the number of STOPP/START and Beers criteria, drug interactions classified based on their potential severity (traffic light system), and adjustment of the medications to other relevant clinical variables.FPs will be able to add and modify patient data in eCRF and able to review again treatment plans as many times as needed with up-to-date relevant information (new drugs, new diagnoses, change if laboratory findings about kidney function, etc.).A specific training tool with video-recorded examples for clinical scenarios with treatment plans reviews appearing on first access to the tool and available for revising when needed as part of the formative intervention.

There are no restrictions regarding concomitant care during the trial. This intervention was developed in accordance with the recommendations and the taxonomy proposed by the Cochrane Effective Practice and Organization of Care Group (EPOC). The intervention is described in detail in Fig. 2, following the approach proposed by Perera et al. and the Template for Intervention Description and Replication (TIDieR) (Additional file 3) [38]..

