### Control group

The patients in the control group will receive the usual clinical care based on the provision of advice and information and will be subjected to the examinations recommended in the guideline corresponding to each of the chronic diseases presented by the patient. Physicians will receive the same initial training programme as professionals in the intervention group.

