#### Primary outcome variable

The primary outcome is a composite endpoint of hospital admission or death during the observation period measured as a binary outcome. Primary outcome measures are recorded by the FPs when they occur or at follow-up visits.

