#### Secondary outcome variables

All cause mortality, non-elective hospital admission (number of episodes and duration)Related to the use of medication: Potentially inappropriate prescription will be evaluated in accordance with the BEER criteria [39] and the STOPP-START criteria [40]; medication safety will be measured as the incidence of adverse reactions and potentially dangerous interactions, classified based on the taxonomy proposed by Otero-López [41] as well as the incidence of adverse reactions; and adherence to treatment will be measured. Medication adherence was measured with the Morisky Medication Adherence score [42].Use of health services will be measured using records of unplanned and/or preventable hospitalizations as well as the use of emergency services and PC (FP and nurse).Quality of life will be measured using the EQ-5D-5L questionnaire [43, 44]. The differences in utility index between the intervention group and the control group at 18 months of follow-up will be used to determine the QALYs gained due to the intervention. The scores or utilities derived from the latest version of this tool, the EQ-5D-5L, have been proposed to provide information on economic evaluations of technologies.Disability will be measured using the WHODAS questionnaire [45] and number of fractures.For cost-utility, the National Health Service perspective will be adopted, with a time horizon of 2 years and a discount rate of 3%. The costs incurred will be the time dedicated to training required by the training programmes, the cost of the teaching staff, the time dedicated to doctor-patient interviews, and the rights to use of the tool (DSS). All costs derived from the intervention will be charged through an opportunity cost proxy: average salary by professional category. As “avoided costs” of the intervention, we will consider the price of the drugs discontinued (measured using the retail price) and the cost of the adverse reactions avoided. The EQ-5D-5L questionnaire will be used to estimate the utilities in both groups (intervention and control). The QALYs obtained with the intervention will be calculated and compared with the difference between the costs incurred and avoided.DSS usability will be measured from user analysis perspective and usability testing [46] to the direct users (FPs): (a) User analysis: this analyses user behaviour while interacting with a website. It is going to be realized non-obtrusively in the background by recording mouse movements and click behaviour to identify to what extent functions and website areas are accessed when reviewing treatments (Hotjar Tool); (b) usability using an ad hoc design with the Spanish-validated System Usability Scale (SUS) [47] and Computer Software Usability Questionnaire [48], DSS acceptability will be measured using records of actions performed with the CheckTheMeds® algorithm (number of changes) and a review of time invested per professional, and DSS satisfaction will be measured using an ad hoc questionnaire.

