#### Calculation of the cost-utility ratio

A cost-utility ratio will be estimated by dividing the total costs by the sum of the potential gains expressed in QALYs. A multivariate sensitivity analysis will be performed by varying the value of the costs with the appropriate distributions within the range of uncertainty. The benefits (QALYs) will also vary with the most suitable distribution in the 95% CIs of the estimates. It will also be included in the sensitivity analysis.

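### The listed cost items do not give the incremental cost of the intervention against this trial's own control arm, and the cost-utility numerator is defined in two ways

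*Protocol article*

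**What the plan says.** All references are to the Protocol article.

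- **Objective.** Aim (Secondary) asks for the cost-utility of the intervention relative to usual care. Secondary outcome variables adopts the perspective of the National Health Service.
- **Costs charged.** "The costs incurred will be the time dedicated to training required by the training programmes, the cost of the teaching staff", followed by physician-patient interview time and the rights to use the DSS.
- **Costs credited.** As avoided costs, "we will consider the price of the drugs discontinued (measured using the retail price) and the cost of the adverse reactions avoided".
- **Who is trained.** Intervention: "All participating physicians will receive this training with the objective of incorporating patient-centred interviews into their routine clinical practice". Control group: "Physicians will receive the same initial training programme as professionals in the intervention group". One training element appears under Intervention group only: "A specific training tool with video-recorded examples for clinical scenarios".
- **What is collected.** "Use of health services will be measured using records of unplanned and/or preventable hospitalizations as well as the use of emergency services", and also primary-care contacts with physician and nurse. Table 1 schedules hospitalizations at 12 and 18 months, health-service use at 6, 12 and 18 months, and the drug treatment plan at every visit. Primary outcome variable: "The primary outcome is a composite endpoint of hospital admission or death during the observation period measured as a binary outcome".
- **The ratio.** The section headed Calculation of the cost-utility ratio gives this rule: "A cost-utility ratio will be estimated by dividing the total costs by the sum of the potential gains expressed in QALYs". Secondary outcome variables instead sets the QALYs obtained against incurred minus avoided costs, and takes QALYs gained from the utility difference between the arms.

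**The concern.** A cost-utility ratio for one arm against another needs a numerator and a denominator that describe the same contrast. Here the denominator is the between-arm QALY difference. Both arms receive the initial training, and the Intervention section says this is deliberate, so that the training effect can be separated from that of the DSS. The QALY difference therefore carries no benefit from the shared training, yet its cost is not excluded from the numerator.

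The credit side has the opposite kind of gap. The trial is designed around a reduction in admissions or deaths, but admissions are not among the avoided costs unless they enter through adverse reactions. Drugs are counted in one direction only, although the DSS output described under Intervention group includes START criteria, which point to omitted treatment, and the Background counts insufficient prescribing as inappropriate.

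At stake is the reported cost per QALY, which is part of the trial's headline objective in the Abstract. The primary effectiveness analysis is not affected.

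**Working it through.** **Step 1. Compare the stated numerator with the between-arm cost difference.** Read every item, favourably to the plan, as a per-patient difference between arms, except the shared training, which is charged in full:

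- T = shared initial training
- S = DSS-specific training
- I = interview time
- L = DSS rights
- D = saving from drugs stopped
- G = cost of drugs started
- R = cost of adverse reactions avoided
- H = saving on admissions, emergency and primary-care contacts not already in R (negative if contacts rise)

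Numerator in Secondary outcome variables: N = T + S + I + L − D − R.

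Between-arm difference, in which T cancels: C = S + I + L + G − D − R − H.

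Error: **N − C = T + H − G.**

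T makes the intervention look too costly. So does H when it is positive. G makes it look too cheap. The sign of the sum cannot be fixed in advance.

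**Step 2. Compare the two definitions of the numerator.** If the total in Calculation of the cost-utility ratio is read literally as the costs charged, it equals T + S + I + L. It then exceeds the netted version by D + R, so the two sections give the same answer only if D + R = 0.

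**Step 3. Scale of what is left out.** The cost-utility plan states no figure to reproduce. The design effect used for scale can be checked from Sample size: 16% incidence, a 6-point difference (so 10%), 80% power and 5% alpha, taken as two-sided, with pooled variance and no continuity correction.

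- Mean proportion = (0.16 + 0.10)/2 = 0.13
- n = [1.960 × √(2 × 0.13 × 0.87) + 0.842 × √(0.16 × 0.84 + 0.10 × 0.90)]² / 0.06² = **492 per group**, as stated
- 984 × 1.08 = 1,063, and 1,063 × 1.08 = 1,148, as stated (574 per group)

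At that effect:

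- 574 × 0.06 = 34.4, about **34 fewer intervention-arm patients** with an admission or death
- after 8% loss: 574 × 0.92 × 0.06 = 31.7, about **32**

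The division between admissions and deaths is not given. The endpoint is binary, so repeat admissions are not counted. These figures give the scale of events and are not a count of admissions saved.

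**Step 4. Scale of the training charge.** If shared training costs t per physician, it adds t divided by the patients per physician. Sample size states an average of eight but uses 5 in the design-effect formula, so the charge is t/8 = 0.125t or t/5 = 0.20t per patient. The documents give no t.

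**Step 5. Monetary size.** No unit costs are stated for training, admissions, contacts or drugs, so no corrected ratio can be computed.

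**The case against.** The best defence is that the variables section already describes an incremental approach. It nets incurred against avoided costs, it takes QALYs as a between-arm difference, and the objective is framed against usual care. The total in the ratio section may be loose wording for that net sum. This stands: a reader might infer that the plan simply uses a total instead of an incremental ratio, and the documents do not support that. They support a conflict between two sections that has to be reconciled.

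Second, the training charged may include the DSS training tool offered to the intervention group only, which is a proper incremental cost. This also stands. It would be too strong to say that all training costs cancel; only the shared initial programme does. A health system adopting the whole package would pay for that programme too, but this does not rescue the charge, because the trial's QALY difference excludes the programme's benefit.

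Third, adverse reactions avoided could include drug-related admissions, a plausible route for a prescribing intervention. This stands in part. It rules out the claim that every admission saving is omitted, and it creates a risk of double counting if admissions are added carelessly. It does not cover other admissions or routine contacts.

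Fourth, an article condenses the full protocol. That does not answer the point, because the article states specific lists of what is charged and what is credited, and those lists give the wrong increment if followed.

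**Conclusion.** The point holds in a limited form. As listed, the costs are not the incremental cost of the intervention against this control arm, for three reasons: shared training is not excluded, collected service use is not costed apart from anything inside adverse reactions, and drug costs run one way. Separately, the numerator is defined differently in two sections.

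The net error is T + H − G in the notation above. Neither its sign nor its size can be determined from the documents. The only scale available is about 34 of 574 fewer intervention patients with an admission or death (about 32 after 8% loss), which assumes that the design effect is achieved and leaves the admission share unknown.

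A reader might go further and conclude that the cost-utility objective cannot be answered. The documents do not support that: service use and treatment plans are scheduled for collection, so the costing can be corrected before analysis. This is a should-fix matter for one secondary objective.

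**What to change.** Rewrite the costing rule so that the same items are costed in both arms from randomisation:

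1. Cost the recorded admissions, emergency contacts and primary-care contacts.
2. Cost all prescribed drugs, started as well as stopped, from the treatment plans.
3. Add interview time, DSS rights and the DSS-specific training.
4. Leave the shared initial training out of the increment.
5. State how an admission already costed as an adverse reaction is handled, so that it is counted once.
6. Use one definition in both sections: the between-arm difference in cost divided by the between-arm difference in QALYs, with uncertainty that respects clustering by family physician.

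The price is a little more costing work. It consists of applying unit costs to service use and prescriptions that the visit plan already collects. The change should be made before any comparison of costs by arm.

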
#### Explanatory and adjustment variables

a) Patient variables (first level)
Sociodemographic: age, sex, nationality, region of residence, marital status, socioeconomic status (monthly salary expressed as multiples of minimum wage), family composition (number of people living in the household), indicators of subjective urban vulnerability, based on those collected by the National Health Survey to explore participants’ neighbourhood (noise level, odours, poor-quality drinking water, unclean streets, air pollution, lack of green areas, feral animals and crime), social support (Duke-UNC-11 Questionnaire adapted to Spanish [49]), profession, and social class [50].Morbidity: number and description of chronic diseases based on the International Classification of Diseases in Primary Care (ICPC) as per O’Halloran list [51].Pharmacotherapeutic treatment plan: number and type of drugs prescribed and active ingredient and dose of each drug.

b) FP variables (second level)
Sociodemographic: age and sex.Professional performance: years of professional experience, resident mentor (yes/no), and average workload measured as average daily consultations per FP during the year prior to the start of the study.

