### Variables

FPs will provide their data before the start of the study. Patient data will be collected by the recruiting FP, who will also be responsible for patient follow-up. All information will be recorded in a case report form designed for the study. Each FP will access the form from their personal computer through the project website using a personal identification code. Four visits were defined for patient data collection: baseline (T0), 6 months (T1), 12 months (T2), and 18 months (T3) (see Table 1).

**Table 1 Tab1:** Visit plan

	T0 (baseline)		T1 (6 m*)	T2 (12 m*)	T3 (18 m*)	Responsible entity
Confirm inclusion/exclusion criteria	X					FP
Written informed consent	X					FP
Sociodemographic variables	X					FP
Morbidity variables and drug treatment plan	X		X	X	X	FP
Randomization of FP´s		X				RU
FP intervention (intervention group)		X				RT
Patient intervention (intervention group)			X	X	X	FP
Mortality				X	X	RT/FP
Hospitalizations				X	X	RT/FP
Functionality (WHODAS), falls, hip fractures			X	X	X	FP
Use of health services			X	X	X	RT
Quality of life	X			X	X	FP
Usability, adhesion, satisfaction			X		X	TG
Costs					X	RT

*T* time, *FP* family physician, *RU* research unit, *IG* intervention group, *RT* research team, *TG* technical group, *m** months from randomization

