#### Analysis of secondary effectiveness

The same analysis will be performed for 12 months. Missing data for professionals and/or patients will be replaced with the most recent reference or available data. For the remaining secondary effectiveness analyses, the difference in means or proportions will be calculated based on the characteristics of the variables (T3−T0) and (T2−T0) between groups using the appropriate statistical tests, and an explanatory model will be adjusted using the same methodology applied to the main outcome variable.

*Estimated quality-adjusted life years (QALYs)* gained at the population level, with corresponding 95% CI, as determined using parametric methods and bootstrap techniques. Given the 2-year time horizon, a discount rate of 3% will be applied.

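### Secondary outcomes are to be contrasted as T3−T0 and T2−T0, but Table 1 schedules no T0 value for service use, WHODAS, falls or hip fractures; prior admission is also absent from the listed covariates

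*Protocol article*

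**What the plan says.** The Variables section defines four collection points, "baseline (T0), 6 months (T1), 12 months (T2), and 18 months (T3"). Table 1 then assigns each measure to visits:

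- "Use of health services" is marked at T1, T2 and T3, with the research team responsible.
- "Hospitalizations" is marked at T2 and T3.
- "Functionality (WHODAS), falls, hip fractures" is marked at T1, T2 and T3.
- Quality of life, and the row for morbidity and drug treatment, do carry a T0 mark.

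Under Secondary outcome variables, service use is a named outcome taken from existing data: "Use of health services will be measured using records of unplanned and/or preventable hospitalizations", together with emergency and primary care contacts. Under Analysis of secondary effectiveness, one rule covers every secondary outcome beyond the 12-month repeat of the main analysis: "the difference in means or proportions will be calculated based on the characteristics of the variables", with T3−T0 and T2−T0 named as the contrasts.

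The primary model (Analysis of main effectiveness) adjusts for baseline patient and physician variables. At patient level, Explanatory and adjustment variables lists sociodemographic items, morbidity ("number and description of chronic diseases based on the International Classification of Diseases in Primary Care (ICPC") and the drugs prescribed. It lists no earlier admission and no patient-level service use.

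**The concern.** There are two linked gaps. First, the analysis rule needs a value at T0 that the visit plan does not schedule for several outcomes. An analysis plan can choose another contrast, but it cannot supply a measurement that was never collected. If this is left open, the contrast actually used for WHODAS, falls, fractures and service use will be settled after the data are in.

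Second, the primary outcome consists of hospital admission or death, yet whether the patient was recently admitted is not among the listed covariates. It is a plausible prognostic variable, available from the same kind of record that already supplies service use. Leaving it out gives up some precision in the adjusted analysis and an auxiliary variable for the planned multiple imputation.

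**Working it through.** **Schedule against analysis rule**

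| Outcome | T0 mark in Table 1 | T3−T0 as a change score |
|---|---|---|
| Quality of life | yes | computable |
| WHODAS | no | not computable |
| Falls, hip fractures | no | not computable |
| Use of health services | no | not computable |
| Hospitalizations | no | not computable |

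Other rows of the same table have T0 marks, so the empty cells are not a fault in how the table was read. The nearest items elsewhere do not fill the gap. Eligibility requires at least one contact with the family physician in the last year, which is a yes/no entry condition. Workload in the previous year is a physician-level variable.

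**The plan's own sample size**

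Inputs from Sample size: 16% against 10% (a difference of 6 points), two-sided alpha 5%, power 80%. The pooled-variance formula without continuity correction gives 492 per arm, 984 in total, as printed. Then 984 × 1.08 = 1062.7, so 1063; and 1063 × 1.08 = 1148.04, so 1148. The printed figures reproduce.

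**Unadjusted power at 1148 patients**

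Effective n per arm = 574 × 0.92 / DE.

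Power = Φ{[0.06 − 1.96·√(2 × 0.13 × 0.87/n)] / √[(0.16 × 0.84 + 0.10 × 0.90)/n]}.

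- DE 1.08 (printed, cluster size 5): n = 489.0, power 79.8%.
- DE 1.14 (the eight patients per physician in the text, 1 + 7 × 0.02): n = 463.2, power 77.6%.

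**Adding prior admission**

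The documents give neither the prevalence q of prior admission nor its odds ratio (OR) for the outcome. Both are assumed: q = 10–30%, OR = 2–5. With mean event rate 0.13, solve (1−q)p0 + q·p1 = 0.13 at the given OR. Then R² = q(1−q)(p1−p0)² / (0.13 × 0.87), and the effective n becomes n/(1−R²). This is an approximation that treats the covariate as removing a share R² of the outcome variance.

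Example, q = 20%, OR = 3: p0 = 0.10, p1 = 0.25, R² = 0.16 × 0.0225 / 0.1131 = 0.032; n = 463.2/0.968 = 478.5; power 78.9%.

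| q | OR | R² | Power, DE 1.08 | Power, DE 1.14 |
|---|---|---|---|---|
| none | – | 0 | 79.8% | 77.6% |
| 10% | 2 | 0.007 | 80.0% | 77.9% |
| 20% | 3 | 0.032 | 81.0% | 78.9% |
| 30% | 4 | 0.056 | 82.0% | 79.9% |
| 30% | 5 | 0.076 | 82.8% | 80.7% |

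The gain is about 0.3 to 3 points. The calculation leaves out the disease and drug covariates already planned, which probably carry part of the same information, so the added gain would be smaller.

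**Change score or covariate, once a baseline exists**

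With equal variances and pre-post correlation ρ (assumed), the variance relative to a follow-up-only comparison is 2(1−ρ) for a change score and 1−ρ² with the baseline as covariate:

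- ρ = 0.3: 1.4 and 0.91
- ρ = 0.5: 1.0 and 0.75
- ρ = 0.7: 0.6 and 0.51

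A raw change loses precision when ρ is below 0.5. It would also subtract a 12-month count from an 18-month count.

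**The case against.** A reader might infer that service use cannot be analysed at all. The text does not support that. The same rule is applied to all-cause mortality, which can have no T0 value, so for events the notation can be read as what accrued between T0 and T3. On that reading, counts from records need no baseline, and falls and fractures can be handled in the same way. This stands, although the protocol does not say so. It does not rescue WHODAS, where a difference from T0 needs a T0 score.

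A reader might also infer that the primary model is wrong because it lacks a strong predictor. The documents nowhere state how predictive prior admission is. The model already has age, sex, chronic diseases and drugs, and an analysis plan that is not shown may add covariates. Omitting one candidate is not an error, so this half is an improvement only.

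Nor should the covariate be presented as repairing the design effect, where the text says eight patients per physician and the formula uses five. That is a separate matter. At DE 1.14, power passes 80% only at the top of the assumed range (OR 5 with prevalence of 20% or more).

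Finally, the look-back year is imperfect. The trial was suspended from March 2020 to May 2021 while services were reorganised. For anyone randomised before about May 2022, a 12-month window reaches into that suspension, and use in that period may predict later use less well. This is a genuine limit on the benefit.

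**Conclusion.** The point holds as a low-severity improvement. The firm part is internal: Table 1 and the secondary analysis rule do not fit together for outcomes without a T0 mark. WHODAS is the plainest case; service use, falls and hip fractures are affected if the contrast is a change score. The softer part is that prior admission is missing from the listed covariates. Its value is modest, about 0.3 to 3 points of power under assumed prevalence of 10–30% and odds ratio of 2–5, and less after the covariates already planned. The gain applies to the adjusted model, not to a crude difference in percentages.

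**What to change.** 1. When the research team extracts service use, also extract hospital admission (yes/no) and counts of service use for the 12 months before randomisation, and show this as a T0 entry in Table 1. Anchor the window to randomisation for everyone, including patients recruited before the suspension.
2. Prespecify prior admission as a covariate in the primary model.
3. Analyse service use as follow-up counts with the prior count as covariate and follow-up time accounted for, not as a raw change.
4. For outcomes that will have no T0 value, such as WHODAS, reconcile Table 1 with the analysis rule by stating that follow-up values are compared between arms. State that falls and hip fractures are events accrued since randomisation.

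The cost is a small amount of extra extraction from records the research team already reads, with no added visit or procedure, plus a check that consent and ethics approval cover the earlier window. The drawback is the look-back year's overlap with the pandemic disruption, which should be acknowledged when the covariate is described.
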